#### 4.2.2 Exclusion criteria

Individuals who meet one or more of the following conditions will be excluded:

1. Diagnosis of atypical or secondary parkinsonism;
2. Hoehn and Yahr stage greater than 2;
3. Presence of severe neurological or psychiatric diseases that compromise the ability to participate in study procedures;
4. Diagnosis of previous dementia;
5. Presence of comorbidities such as active neoplasms, chronic obstructive pulmonary disease, heart failure and/or chronic kidney failure.
6. History of gastrointestinal neoplasms, inflammatory bowel diseases or surgeries involving the gastrointestinal tract;
7. Constipation secondary to clinical conditions, such as hypothyroidism or diabetes mellitus;

8. Opioid use;
9. Use of probiotics or antibiotics in the last 3 months;
10. Continuous use of laxatives in the last 8 weeks;
11. Presence of severe dysphagia according to the Functional Oral Intake Scale (FOIS) classification;
12. Individuals using enteral or parenteral nutrition;
13. Individuals receiving nutritional follow-up in the last 3 months.

#### 4.2.3 Risks and Benefits

- Risks: Participation in the research does not involve known significant risks. However, discomfort may arise from the time taken to respond to the questionnaires and evaluations, considering that each visit to the CPC will last approximately 1 hour and 30 minutes. Furthermore, some instruments include questions of a personal nature, which may generate embarrassment or discomfort. Anthropometric measurements and the walking test, although non-invasive, may eventually cause some physical discomfort. It is important to emphasize that all adopted procedures are non-invasive.
- Benefits: Potential benefits for the participant include access to detailed information about their nutritional status, through assessments of food intake and body composition (muscle mass, fat, and water). Participants will also receive individualized nutritional guidance performed by a nutritionist, provided at the beginning or end of the study, contributing to a greater understanding and management of their eating habits. From a collective point of view, participation will help expand scientific knowledge about the relationship between diet and health in people with PD, enabling the development of more effective care and nutritional guidance strategies in future contexts.

#### **4.3 Randomization and blinding**

Randomization will be performed by an independent researcher, not involved in data collection or clinical evaluations. The method used will be simple, computer-generated randomization, in a 1:1 ratio, using a random number table. The parallel groups are: (1) intervention group, which will receive a food plan, dietary guidance and follow-up with a nutritionist, and (2) control group.

The researcher responsible for the final evaluations will be blinded to the participants' allocation. Similarly, the professionals responsible for microbiota sequencing and analysis, as well as the statistician in charge of data analysis, will also remain blinded. Participants' randomization will occur after the initial evaluation, so blinding of the researchers responsible for this initial step will not be necessary. However, the researchers involved in the nutritional intervention will not be blinded,

since this measure is not necessary; furthermore, they will be responsible for the evaluations carried out on days 45 and 90 of the study.

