#### **4.5 Sample Size**

A sample size of 48 subjects (24 for each group) was calculated to test whether there is a minimum difference of 1 bowel movement/week between the mean bowel movements per week of the intervention and control groups at the last time point (week 12) of the repeated measures study (with the addition of 10% for possible losses and refusals, this number should be 54, 27 for each group). The calculation considered 80% power, a significance level of 5%, a standard deviation of 1.15 and 1.21 bowel movements/week for the intervention and control groups, respectively (Rusch et al., 2024). As well as 90% retention at time points 2 and a permutable correlation matrix with a correlation of 0.5. This calculation was performed using the PSS Health online tool (Borges et al., 2020).

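### Simple randomisation of 54 leaves entry bowel frequency, the starting level of the primary outcome, unbalanced and outside the listed covariates; stratified blocks are a cheap improvement

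*Protocol*

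**What the plan says.** Section 4.3 fixes the method: "The method used will be simple, computer-generated randomization, in a 1:1 ratio, using a random number table". It names no blocks, strata or minimisation factors. An independent researcher performs the randomisation, after the initial evaluation. The staff who deliver the intervention are not blinded.

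Section 4.5 plans equal arms: "A sample size of 48 subjects (24 for each group) was calculated", and then "with the addition of 10% for possible losses and refusals, this number should be 54, 27 for each group". The target is "a minimum difference of 1 bowel movement/week between the mean bowel movements per week of the intervention and control groups" at week 12.

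The primary outcome is weekly bowel movement frequency, taken from the participant's diary (Sections 4.4 and 4.7.1). Entry needs any two of the listed Rome IV items, and a frequency under three spontaneous movements a week is one of them (Section 4.2.1). Section 4.8 specifies a mixed model with group, time and their interaction. It adjusts every model for age, sex, disease duration and levodopa-equivalent dose, and for weekly laxative use over time. Entry bowel frequency is not on that list.

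**The concern.** Two things are left to chance in a trial of 54.

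The first is arm size. A 1:1 ratio under unrestricted allocation holds only on average, while the sample size is laid out as equal arms.

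The second matters more. Because low frequency is optional at entry, the trial will mix people who start low with people who start in the normal range. That starting level should be among the strongest predictors of the outcome, and Section 4.5 itself assumes a correlation of 0.5 between time points. Participants know their allocation and complete the diary themselves, so a visible entry difference between arms would be hard to explain away. Once allocation is complete, it cannot be designed out.

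**Working it through.** **Inputs.** Section 4.5 gives a difference of 1 movement per week, SDs of 1.15 and 1.21, 80% power, 5% significance, 90% retention at time point 2, correlation 0.5, and 48 participants raised to 54. Assumed here: a two-sided test, equal loss in both arms, and the prevalences named below.

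**1. The plan's own figure.**
- n per arm = (1.15² + 1.21²) × (1.960 + 0.842)² = 2.7866 × 7.849 = 21.87.
- Variance factor for the last time point: 0.5² + (1 − 0.5²)/0.9 = 1.083.
- 21.87 × 1.083 = 23.69, so 24 per arm. 48/0.9 = 53.3, raised to 54.

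The stated 24 and 27 per arm reproduce.

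**2. Arm sizes under simple randomisation, Binomial(54, 0.5).**
- Exactly 27:27: 10.8%.
- Both arms at least 24: 65.9%. Smaller arm below 24: 34.1%.
- Smaller arm 20 or fewer: 7.6%. Central 95% range for one arm: 20 to 34.

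**3. Power cost.** SE = √(1.15²/n₁ + 1.21²/n₂), with 10% loss taken from each arm and noncentral t:

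| Split (intervention:control) | Power |
|---|---|
| 27:27 | 82.4% |
| 24:30 | 82.2% |
| 22:32 | 81.5% |
| 20:34 | 80.3% |
| 18:36 | 78.5% |

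Averaged over all splits, power is 81.7%, against 82.4% when balanced: a cost of 0.7 points. A split that takes power below 80% arises in 5.8% of trials by this method, 2.5% by the normal approximation and 1.2% with the repeated-measures factor.

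**4. Imbalance in a binary entry factor.** Chance that the arms differ by 20 percentage points or more, by simulation:

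| Allocation | Prevalence 50% | Prevalence 30% |
|---|---|---|
| Simple | 14.2% | 11.2% |
| Fixed 27:27, not stratified | 13.4% | 10.1% |
| Blocks of 2, 4 or 6, stratified on the factor | none in 20,000 | none in 20,000 |

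The stratified blocks also left no arm below 24.

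**5. What an entry gap does to the result.** Assume that the Section 4.5 SDs also hold at entry.
- The SE of a chance entry difference at 27:27 is √(2.7866/27) = 0.32 movements per week.
- A gap of at least 0.5 corresponds to z = 0.5/0.321 = 1.56, which occurs in about 12% of trials.
- At correlation 0.5, a gap of 0.5 moves the week-12 comparison by 0.5 × 0.5 = 0.25, a quarter of the target effect.
- A change-from-baseline comparison moves by 0.25 − 0.5 = −0.25: the same size, opposite sign.

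**6. Precision.** Take entry frequency as normal and split at its median. The squared correlation between a normal variable and its median split is 2/π = 0.637. The split then explains 0.5² × 0.637 = 0.159 of the outcome variance, and the SE falls by the factor √(1 − 0.159) = 0.917, about 8%. Simulation of the stratified design gave 0.325 falling to 0.297, about 9%. Adjusting for the same factor under simple randomisation also brings the SE to about 0.30. Most of the precision therefore comes from the model term, and stratification adds the balance in the arms as randomised.

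**The case against.** Simple randomisation is a legitimate method. The 1:1 ratio describes the allocation probability and 27 per group is a planning target, so Sections 4.3 and 4.5 do not contradict each other. In an open single-centre trial whose intervention staff know past allocations, it is also the least predictable choice. All of that stands.

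A reader might infer that the arms will usually fall short of 24, so that the sample size fails. The figures do not support this. Both arms reach 24 in about 66% of trials, power depends on both arm sizes together, and it stays at or above 80% down to about 20:34. Reading 24 as completers does not rescue the inference. The 24 already allows for 90% retention, and with independent 10% loss even a fixed 27:27 gives 24 completers in both arms only 51.5% of the time (20.7% under simple randomisation).

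A reader might also charge the 14% imbalance to the lack of blocking. Blocking alone leaves 13.4%; only stratification on the factor removes it.

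The best counter-argument on entry frequency is that the group-by-time interaction absorbs an entry difference if baseline is a modelled time. This stands in part. The interaction subtracts the entry gap, but at a correlation of 0.5 that over-corrects by half the gap (step 5). The covariates that Section 4.8 does list answer the worry for those factors, not for entry frequency.

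**Conclusion.** The point holds as a cheap design improvement. Unequal arms cost about 0.7 points of power on average, which alone would not justify a change. The stronger reason is that the starting level of the primary outcome is neither balanced by design nor among the covariates Section 4.8 names. A 20-point or larger imbalance in low entry frequency arises in about 14% of trials at an assumed 50% prevalence (11% at 30%). Balancing and modelling that factor would lower the SE of the main comparison by about 9%.

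Nothing here makes the comparison biased or invalid, and the documents do not support calling it a sample-size error. The figures assume a two-sided test, equal loss by arm, entry SDs equal to those in Section 4.5, the planned correlation of 0.5 and, for precision, a split near the median. A statistical analysis plan, not shown, could add baseline frequency to the model. It could not supply balance at allocation.

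**What to change.** For participants not yet randomised, replace simple randomisation in Section 4.3 with computer-generated permuted blocks of randomly varying, undisclosed size, stratified by entry frequency (under three spontaneous movements a week, yes or no). State that the independent researcher keeps the list. The item is already asked for eligibility, so it is known before allocation, and two strata are workable with 54 participants at one site.

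In Section 4.8, add the entry-frequency stratum or baseline frequency to the primary model. If baseline is kept as one of the modelled times, enter the stratum with its interaction with time, because a time-constant main effect does not alter a change contrast.

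The cost is a sentence in each section and a new list. The downside is slight predictability near the end of a block for staff who know past allocations, limited by varying and concealing the block sizes. If enrolment is too far advanced for a new list, the model term alone recovers most of the precision.

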#### **4.6 Procedures by groups**

The individuals included in the study will undergo the complete initial assessment (baseline) and will then be randomized into control or intervention groups. After randomization, participants will return to the CPC within 7 days (D0) for stool sample delivery, and participants in the intervention group will receive nutritional guidance.

At 45 days (D45), dietary intake and constipation will be assessed via telephone. At the end of the study (D90), participants will be called to return to the CPC for the complete final assessment. At this time, if positive, participants in the control group will receive complete nutritional guidance. The researchers responsible for the final assessment and data processing will be exclusive to these tasks and will not have access to randomization and group allocation information.

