- Nova Ultra-processed Foods (Nova-UPF), which ranges from 0 to 23 points and reflects the consumption of ultra-processed foods.
- Adherence to the nutritional intervention

Adherence to the nutritional intervention will be assessed through telephone calls and self-reported compliance with the guidelines, as well as the analysis of food consumption (24h recall). This monitoring will be carried out exclusively by the researcher responsible for the intervention and will be stored separately from the other data. Fiber consumption compared to the goals will be used as one of the indicators of adherence. Participants who meet at least 75% of the goals will be considered to have good adherence.

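### Section 4.3 assigns the D90 final evaluation to the unblinded intervention researchers, contradicting its own blinded final evaluator and the allocation-blind assessors of section 4.6

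*Protocol*

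**What the plan says.** Section 4.3 makes three statements about who evaluates:

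- On the final evaluations: "The researcher responsible for the final evaluations will be blinded" to allocation.
- On the intervention team: "However, the researchers involved in the nutritional intervention will not be blinded".
- On the same intervention team, in the closing clause: "they will be responsible for the evaluations carried out on days 45 and 90 of the study".

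Section 4.6 fixes the timing: "At the end of the study (D90), participants will be called to return to the CPC for the complete final assessment". It adds that those responsible for the final assessment and for data processing "will be exclusive to these tasks and will not have access to randomization and group allocation information". For the midpoint it says: "At 45 days (D45), dietary intake and constipation will be assessed via telephone", without naming who makes the call.

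Section 4.7.3 has a trained nutritionist conduct the 24-hour recall. On adherence, which draws partly on that recall, it says: "This monitoring will be carried out exclusively by the researcher responsible for the intervention".

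**The concern.** The D90 visit is assigned to two sets of people who cannot be the same. Someone who delivers the meal plan knows the arm. That person is neither blinded nor confined to final assessment.

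Participants are not described as blinded, and the control arm receives guidance, if at all, only after D90. For measures that an examiner scores or an interviewer elicits, a blinded assessor is therefore the safeguard against expectation and prompting at the point of data collection. The blinded statistician and laboratory named in 4.3 work downstream and cannot undo an observer effect already in the recorded value. If the nutritionist who set a participant's fibre goal also conducts the D90 recall and the Constipation Scoring System (CSS) interview, a difference between arms may partly reflect how the questions were put.

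**Working it through.** No arithmetic settles this point, so the check sets the passages side by side.

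**Step 1: when the final evaluation takes place.** Section 4.6 puts the complete final assessment at D90. The final evaluations of 4.3 and the day-90 evaluations in its last clause are therefore the same event.

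**Step 2: who performs it.**

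- 4.3, opening statement on blinding: a researcher blinded to allocation.
- 4.6: staff exclusive to final assessment and data processing, with no access to allocation.
- 4.3, last clause: the subject of the sentence is the researchers involved in the intervention, who are stated to be unblinded.

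The first two agree. The third is incompatible with both.

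**Step 3: D45.** The promises of blinding in 4.3 and 4.6 cover only the final assessment. The only statement on who evaluates at D45 is the last clause of 4.3, which names the unblinded team. This is an openly unblinded assessment and not a contradiction. It collects the CSS (4.7.1) and the 24-hour recall and Screener-Nova (4.7.3). Section 4.8 models primary and secondary outcomes with group, time and their interaction, so the D45 values enter the analysis.

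**Step 4: which outcomes are exposed at D90 if the last clause of 4.3 is followed.**

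- Most exposed: MDS-UPDRS Part III, which the evaluator scores (4.7.6); the CSS, if administered by interview; the 24-hour recall, an interview; and the Screener-Nova, whose scores are generated automatically but whose questions the researcher goes through with the participant (4.7.3).
- Less exposed: handgrip strength, a dynamometer reading, and the Timed Up and Go, a timed test (4.7.4). Encouragement and timing can still influence both.
- Not directly exposed: the primary outcome, weekly bowel movement frequency, taken from a diary that participants complete daily (4.4 and 4.7.1); and the microbiota outcomes, whose sequencing and analysis are blinded (4.3).

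**Step 5: where this touches the objectives.** Dietary intake and diet quality are secondary objective 3, and nutritional status is objective 4 (section 3.2). Section 3.2 has no objective for a treatment effect on motor scores, although the abstract lists clinical parameters among the outcomes. The exposure falls on secondary outcomes throughout.

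**Step 6: size.** The documents contain no figure for observer bias on any of these measures. A single assumed shift would not suit instruments as different as a recall interview and a dynamometer, so none is calculated.

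**The case against.** The strongest reply is that the plan's intention is clear. Two statements support a blinded, separate D90 assessor and only one clause says otherwise. That clause may be a slip, perhaps in translation. This stands in part: the certain defect is contradictory text, and unblinded D90 assessment is not shown to be what will happen. But staff working from 4.3 could follow the clause as written, and data collected that way could not be made blind afterwards.

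Four stronger readings are tempting, and the documents do not support them:

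- *The primary result is compromised.* The diary is completed by participants, and the sample size in 4.5 concerns bowel movements at week 12. Blinding the assessor would not change what an unblinded participant writes down.
- *No other blinding exists.* Section 4.3 also blinds the microbiota laboratory and the statistician.
- *D45 is contradicted as well.* No passage promises a blinded D45 assessor, so that is a design recommendation.
- *Adherence monitoring by the intervention researcher breaks the blind.* Section 4.7.3 stores it separately, which helps to protect the blind. Only the shared use of the recall needs clarifying.

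A practical objection also stands. Moving the D45 call to the final assessors would conflict with their exclusive role in 4.6. The recall also requires a trained nutritionist, and the protocol does not say that those assessors include one. A blinded D45 call therefore cannot be assumed to need no extra staff.

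**Conclusion.** The contradiction is real and confined to D90. Section 4.3 conflicts with itself and with 4.6 on who performs the final evaluation, and the passages must be reconciled before D90 data are collected.

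The consequence is conditional. If the last clause of 4.3 governs practice, the examiner-rated and interviewer-administered secondary outcomes at D90 lose their protection against observer bias, and the trial could not truthfully report blinded final assessment. If 4.6 governs, only the wording is wrong. A reader might infer an inflated false-positive rate of some definite size, but any such figure would rest on an assumed shift for which the documents offer no support.

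The conclusion assumes that the last clause means what its grammar says and that the evaluations on day 90 are the final assessment of 4.6. The unblinded D45 call is a separate weakness of lower weight.

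**What to change.** **D90 (necessary).** Remove day 90 from the last clause of 4.3. State there that all D90 assessments, including the recall interview, are performed by the allocation-blind assessors of 4.6, and that participants are asked not to reveal their arm to them. Confirm that these assessors include a trained nutritionist who takes no part in the intervention, since 4.7.3 requires one for the recall. The cost is a change of wording that uses assessors the plan already provides, subject to that confirmation.

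**D45 (recommended).** Where existing staff allow, have an allocation-blind assessor make the D45 call, and amend the exclusive-role wording in 4.6 accordingly. This reassigns one call per participant. Otherwise, keep the present arrangement, report the D45 CSS and diet data as collected unblinded, and base conclusions on secondary outcomes on the D90 contrast.

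**Adherence.** Leave monitoring with the intervention researcher, stored separately as 4.7.3 already provides and with its telephone and self-report sources intact. Add that the D90 dietary outcome is the recall taken by the blinded assessor.

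None of this alters an outcome, a visit, the sample size or the analysis model.

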#### **4.4 Primary Outcome**

The primary outcome of the study is the frequency of bowel movements per week, which will be assessed through the bowel movement diary.

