### **3. OBJECTIVES**

#### **3.1 Primary Objective**

To evaluate the efficacy of a nutritional intervention with dietitian follow-up on the number of bowel movements per week in individuals with Parkinson's Disease and functional constipation.

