#### 4.2.1 Inclusion Criteria

Adults with a prior diagnosis of Parkinson's Disease, confirmed by a neurologist based on the Movement Disorders Society criteria (Postuma et al., 2015), and who have been on a stable dose of levodopa for at least 3 months will be included. Furthermore, participants must report at least two of the criteria defined by the Rome IV protocol for the characterization of Functional Constipation (Drossman; Hasler, 2016):

- Straining during more than 25% of defecations;
- Lumpy or hard stools (Bristol Stool Form Scale types 1–2) in more than 25% of defecations;
- Sensation of incomplete evacuation for more than 25% of defecations;
- Sensation of anorectal obstruction or blockage for more than 25% of defecations;
- Need for manual maneuvers to facilitate defecation (e.g., digital evacuation, support of the pelvic floor) in more than 25% of defecations;
- Fewer than three spontaneous bowel movements (SBM) per week;
- Loose stools are rarely present without the use of laxatives;
- Insufficient criteria for irritable bowel syndrome;

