#### 1. Evacuation Diary

All participants will receive an evacuation diary, which must be filled out daily during the study period. This instrument will allow monitoring the evolution of constipation symptoms throughout the intervention weeks. The registered information includes:

- Number of evacuations per week (evacuation frequency);
- Stool consistency using the Bristol Stool Scale, a validated visual tool that classifies stools into seven types. Types 1 and 2 will be considered hard stools, and their percentage will be calculated over time;
- Straining during evacuation (report of need to strain to evacuate);
- Sensation of incomplete evacuation;

- Use of rescue laxative (in case of absence of spontaneous evacuation).

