#### **4.8 Statistical Analysis**

Individuals will be identified through a number to maintain data confidentiality, and all collected information will be typed into the Microsoft Office Excel® spreadsheet which will be stored on the institutional Google Drive®. Only the responsible researchers will have access to the data. After tabulation, the database will be exported to the SPSS v18.0 software to perform the statistical analysis. Descriptive data analysis will be performed according to the characteristics of each variable: mean and standard deviation or median and interquartile range for quantitative variables, and frequency and percentage for categorical variables.

Intent-to-treat (ITT) analyses will be performed for all outcomes. Primary and secondary outcomes will be analyzed using generalized linear mixed models (GLMM) with group, time, and their interaction as fixed effects, and random intercepts by participants. Age, sex, disease duration, and LEED will be included as baseline covariates in all models. Weekly laxative use will be included as a time-varying covariate to adjust for its potential confounding effect on bowel movement frequency. Missing data will be handled through the likelihood-based estimation inherent to GLMM, which provides valid estimates under the missing at random (MAR) assumption. Sensitivity analyses will be conducted to assess the robustness of results to potential departures from the MAR assumption.

Regarding the microbiota, alpha diversity ( $\alpha$ -diversity) will be evaluated by the Shannon index and statistical significance will be verified by linear modeling for mixed effects. Beta diversity ( $\beta$ -diversity) will be analyzed using Principal Component Analysis (PCA), Principal Coordinate Analysis (PCoA), and Non-metric Multidimensional Scaling (NMDS), all based on Aitchison (Aitchison, 1982) and Jaccard (Jaccard, 1908) distances. Statistical significance and the proportion of explained variance will be assessed using Permutational Multivariate Analysis of Variance (PERMANOVA) (Anderson, 2014) and linear models for mixed effects.

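### The primary outcome counts evacuations that follow rescue laxative, and adjusting for weekly laxative use does not correct for this; the effect is diluted if controls use more rescue

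*Protocol*

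**What the plan says.** The primary objective (section 3.1) is "To evaluate the efficacy of a nutritional intervention with dietitian follow-up on the number of bowel movements per week". Section 4.4 defines the outcome: "The primary outcome of the study is the frequency of bowel movements per week, which will be assessed through the bowel movement diary". The diary item that supplies it (section 4.7.1, Evacuation Diary) is "Number of evacuations per week (evacuation frequency", and section 4.5 sizes the trial on a difference of 1 bowel movement per week at week 12. None of these places sets aside evacuations that follow a laxative.

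The protocol does know the distinction. One entry item in section 4.2.1 is "Fewer than three spontaneous bowel movements (SBM) per week", and the diary also records "Use of rescue laxative (in case of absence of spontaneous evacuation". Section 4.2.2 excludes "Continuous use of laxatives in the last 8 weeks", so occasional users may enter.

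Laxative use is not ignored in the analysis. Section 4.8 states: "Weekly laxative use will be included as a time-varying covariate to adjust for its potential confounding effect on bowel movement frequency".

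**The concern.** Rescue is tied to a failure of the function that the trial studies. A control who has no spontaneous evacuation, takes the laxative and then evacuates adds one to the count, just as an intervention participant does whose bowel function improved through diet. Controls receive no nutritional guidance before D90. If the diet works, they will have more occasions for rescue, so the outcome could understate the benefit precisely when there is one.

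The planned adjustment looks like a remedy, but weekly laxative use is not a confounder of a randomised comparison. It is partly a result of allocation and partly a result of low frequency itself. Adjusting for it compares participants who needed the same amount of laxative, and so removes any benefit that works by reducing that need. At stake is a false negative in a trial sized with almost no reserve above 80% power.

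**Working it through.** **1. The plan's own sample size.** Inputs from section 4.5: difference 1; SDs 1.15 and 1.21; power 80%; significance level 5% (two-sided reproduces); retention 90%; correlation 0.5.

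- Per group without losses: (1.960 + 0.842)² × (1.15² + 1.21²) / 1² = 21.87.
- Retention factor for repeated measures: 0.5² + (1 − 0.5²)/0.9 = 1.0833.
- 21.87 × 1.0833 = 23.69, so 24 per group and 48 in total. 48/0.9 = 53.3, so 54 in two equal arms.

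The stated figures reproduce. There is no arithmetic error in section 4.5.

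**2. Dilution.** Let x be the excess of laxative-induced movements per week in controls over the intervention arm. If the spontaneous difference is 1, the unadjusted difference in total movements is 1 − x. The protocol gives no value for x, so every row with x above zero is an assumption.

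Pooled SD = √[(1.15² + 1.21²)/2] = 1.18. Standard error with 24 per group = 1.18 × √(2/24) = 0.341. Power is for a two-sided 5% two-sample t-test. The total N keeps the step 1 formula, divided by (1 − x)².

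| x | Difference | Power, 24 per group | Total N for 80% power (with 10% losses) |
|---|---|---|---|
| 0 | 1.00 | 82% | 48 (54) |
| 0.2 | 0.80 | 63% | 76 (85) |
| 0.25 | 0.75 | 58% | 86 (96) |
| 0.5 | 0.50 | 30% | 190 (212) |

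With the step 1 formula in place of the t-test, power is 80.5%, 62%, 56% and 29%.

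**3. Does the covariate repair it?** A large-sample simulation (400,000 participants, final week only) assumed a true spontaneous difference of 1.0, SD 1.18 and a control mean of 2.5 or 3.0 per week. Rescue was taken in 25%, 50% or 100% of the weeks with fewer than 3 spontaneous movements. The number of doses was the shortfall rounded up, with 1 or 1.5 evacuations per dose. All of these settings are assumptions. The covariate in this table is the weekly number of doses.

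| Weeks rescued | Evacuations per dose | Control mean | Total, unadjusted | Total, adjusted |
|---|---|---|---|---|
| 25% | 1 | 2.5 | 0.83 | 0.88 |
| 25% | 1 | 3.0 | 0.88 | 0.89 |
| 50% | 1 | 2.5 | 0.67 | 0.74 |
| 50% | 1 | 3.0 | 0.75 | 0.75 |
| 50% | 1.5 | 2.5 | 0.51 | 0.74 |
| 50% | 1.5 | 3.0 | 0.63 | 0.75 |
| 100% | 1 | 2.5 | 0.35 | 0.23 |
| 100% | 1 | 3.0 | 0.51 | 0.37 |

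With any use (yes or no) as the covariate, the adjusted values run from 0.21 to 0.89. Adjustment helps in some settings, harms in others and never returns 1.0.

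**4. Changing the outcome but keeping the covariate.** Write total T = S + kR, with S the spontaneous count, R the weekly doses and k the evacuations per dose. In a linear regression on group and R, the term kR is absorbed entirely by the coefficient of R, so the group coefficient is the same for T and for S. Redefining the outcome while keeping that covariate would leave the adjusted column unchanged. With any use as the covariate, the group difference in spontaneous movements was 0.36 to 0.91, against a true 1.0.

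**The case against.** The strongest reply is that the protocol is consistent and has dealt with laxatives. Sections 3.1, 4.4, 4.5 and 4.7.1 all use total movements, and section 4.8 adjusts for weekly use. Much of this stands, and it rules out several stronger readings.

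- **That the planned analysis simply scores rescue as success.** A reader of section 4.4 alone might infer this. The outcome does so, but the planned model is adjusted. The valid criticism of section 4.8 is that the adjustment is unsuitable.
- **That the effect will shrink.** The documents give no rescue rate. With equal use in both arms the mean difference is unaffected, and an induced evacuation may replace one that would have occurred anyway.
- **That the outcome contradicts the objective.** It does not, since both are total counts. Preferring spontaneous movements is a choice of estimand.
- **That entry is defined by spontaneous movements.** That item is one of a list of which at least two are needed. A participant can qualify on straining and hard stools.
- **That all rescue use reflects failure arising in the trial.** Only continuous prior use is excluded, so some use may be habit in either arm.
- **That the power figures predict this trial.** They come from an unadjusted t-test and treat the planned difference of 1 as a spontaneous difference, whereas section 4.5 states it for the total count.

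The length of an attribution window can be left to a statistical analysis plan. What the primary outcome counts, and the covariate, are already fixed in the protocol.

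**Conclusion.** The point holds in conditional form. As written, the primary outcome credits evacuations that follow rescue laxative, although the protocol foresees rescue when bowel function fails. If controls use more rescue, the difference is diluted, and the covariate in section 4.8 is not a dependable correction and can make the dilution worse.

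The size is unknown. Under the assumptions in step 2, an excess of 0.2 per week (one induced movement every five weeks) already takes power from 82% to 63%, and 0.5 per week takes it to 30%. With no imbalance in rescue there is no loss from the outcome definition. The sponsor should make the change because it is cheap and the trial has little power to spare. It does not correct an error in the sample size.

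**What to change.** 1. In sections 3.1, 4.4 and 4.5, define the primary outcome as spontaneous bowel movements per week: diary evacuations with no laxative intake within a window whose length is fixed before any data are seen.
2. In section 4.7.1, state that the daily diary records evacuations and laxative intake by date, so that the two can be linked. The present text lists them as separate items and does not say this.
3. In section 4.8, remove weekly laxative use as a time-varying covariate from the primary model. Step 4 of the working shows that the first change achieves little without this one.
4. Report total evacuations and rescue-use days by arm as secondary outcomes.

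This costs protocol wording, one derivation rule and possibly a small change to the diary layout. It adds no visit or instrument and does not touch the conditions under which rescue may be taken.

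There are two downsides. The difference of 1 per week and the SDs of 1.15 and 1.21 must be stated as assumptions for the spontaneous count; if they carry over, 24 per group stands. The window will also discard some genuine spontaneous movements in rescue users, which could bias the comparison the other way. The secondary analysis of total evacuations serves as a check on that.
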